Considerable amount of the current literature pays particular attention to the importance of educational intervention for depression literacy.^[11]^ Rahman et al^[12]^ argued that the school programs succeeded in improving awareness of mental health in school children and the community. The school children were receptive to the program, and shared their new understanding with family, friends, and neighbors. An Internet-based intervention study conducted in Australia suggests that brief mental health literacy and destigmatization improves knowledge and may decrease stigma but does not increase help-seeking for young elite athletes.^[13]^ Another study conducted in Sweden suggested that 42.7% of the respondents identified depression. Depression was recognized more often by women than men. Professional help was suggested by a minority of the respondents for managing symptoms of depression.^[14]^ Overall, these studies highlight the need for educational intervention about depression literacy at the school level. As far as we are aware, there is no similar study conducted in Jazan area that deals with depression.

The main objective of this study is to measure the effect of an educational intervention program about depression on depression literacy and stigma among secondary schools in Jazan City, during the academic year of 2016.

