#### Phase three

2.3.3

Post-intervention assessment by the D-Lit, DSS, and SSDS questionnaires will be conducted for the control and intervention groups immediately after the intervention and during a follow-up after 3 and 12-months.

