### Statistical analysis and data management plan

2.4

The main analysis will include the data collected from all respondents. Differences between socio-demographic variables will be examined using chi-squared analyses. The Statistical Package for the Social Sciences (SPSS) (version 20) will be used to analyze the data. Differences between mean scores of D-Lit, DSS, and SSDS for the intervention and control groups—as well as changes in mean scores over time for each group—will be tested with either a paired *t* test or with Welch *t* test when the variances of the 2 comparison groups are not equal. To examine differences between groups at the baseline, Student *t* test—or the Mann–Whitney *U* test if appropriate—will be performed for pre-intervention D-Lit, DSS, and SSDS scores. All tests will be adjusted for cluster design using the design effect.^[28]^*P*-values <.05 will be used in all analyses.

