### Expected outcome

2.5

The expected outcome of this study is an increase in depression literacy among secondary school students in the intervention group.

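### Section 2.4 chooses between a paired and a Welch t test by variance instead of by pairing, and tests change only within each arm, with no between-arm test of change or baseline-adjusted contrast

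*Protocol article*

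**What the plan says.** All references are to the protocol article.

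- **Aim (Introduction).** The study is to "measure the effect of an educational intervention program about depression on depression literacy and stigma among secondary schools in Jazan City".
- **Assessments (2.3.1 and 2.3.3).** Both arms complete the three scales (D-Lit, DSS, SSDS) before the programme and again "immediately after the intervention and during a follow-up after 3 and 12-months".
- **Comparisons (2.4).** One sentence names two: "Differences between mean scores of D-Lit, DSS, and SSDS for the intervention and control groups", and, in a parenthetical addition, "as well as changes in mean scores over time for each group".
- **Test rule (2.4).** The same sentence says that these are to be "tested with either a paired *t* test or with Welch *t* test when the variances of the 2 comparison groups are not equal".
- **Baseline (2.4).** This has its own rule, with independent-sample tests: "To examine differences between groups at the baseline, Student *t* test" or Mann-Whitney.
- **Clustering (2.4).** "All tests will be adjusted for cluster design using the design effect".
- **Expected outcome (2.5).** "The expected outcome of this study is an increase in depression literacy among secondary school students in the intervention group".

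**The concern.** Whether a test should be paired is a matter of design: are the two sets of scores from the same students or from different ones? Equality of variances is a separate question, and it arises only once the samples are known to be independent. The rule in 2.4 uses the second question to settle the first, and does so for two comparisons that need different answers.

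The second weakness concerns the effect of the programme. Change is tested arm by arm, and the expected outcome mentions only the intervention arm. A report that follows this wording could present a significant rise in the intervention arm, perhaps beside a non-significant one in the control arm, as evidence that the programme works. Neither pattern is a test of the difference between arms. With 3 scales, 3 post-intervention times and 2 arms there are 3 × 3 × 2 = 18 within-arm comparisons with baseline, and none of them alone estimates the randomised contrast.

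**Working it through.** **1. The rule set against the data structure**

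| Comparison | Data | Suitable type of test | Literal rule, variances equal | Literal rule, variances unequal |
|---|---|---|---|---|
| Intervention vs control after the programme | Different students in different schools (2.2) | Independent-sample | Paired: no pairs exist | Welch: suitable type |
| Change within one arm | Same students, repeated | Paired | Paired: suitable type | Welch: ignores the pairing |

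The rule fails in one cell of each row. Student's t test is named for baseline only, so no independent-sample test is named for the post-intervention comparison when variances are equal.

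**2. What the sample size was built for**

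Inputs from 2.2: effect size 0.5, alpha 5%, ICC 0.02, 10% loss, 180 per arm. From 2.3.2.1: 90 students per school, hence 81 after 10% loss. Power is not stated; 80% two-sided is assumed.

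- Unadjusted two-group size: 63 per arm.
- Design effect: 1 + (81 − 1) × 0.02 = 2.60.
- 63 × 2.60 = 163.8, so 164 per arm; 164 / 0.9 = 182.2, so 183 per arm, 366 in total. The plan says 360.
- Reverse check: 162 evaluable per arm is 162 / 2.60 = 62.3 effective, which gives 79.7% power.

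On these assumptions 360 fits a two-arm comparison. The test rule does not alter it.

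**3. Cost of using Welch on pre/post scores**

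With equal variance σ² at both times and pre/post correlation r, the variance of a student's change is 2σ²(1 − r). An independent-sample test uses 2σ². The ratio of standard errors is 1/√(1 − r), and the true level of a nominal 5% test is 2 × [1 − Φ(1.96 × ratio)].

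| Assumed r | SE ratio | True level |
|---|---|---|
| 0.3 | 1/√0.70 = 1.20 | 1.9% |
| 0.5 | 1/√0.50 = 1.41 | 0.6% |
| 0.71 | 1/√0.29 = 1.86 | 0.03% |

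The value 0.71 is the D-Lit test-retest figure in 2.3.1, borrowed as a pre/post correlation. The error is conservative and touches only within-arm tests.

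**4. What a within-arm test shows when there is no effect**

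Assume the same rise in both arms, no intervention effect, r = 0.71 and 162 students per arm. The size of the rise is an assumption, so two values are shown. Simulation (20,000 runs, clustering ignored):

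| Common rise | Intervention arm significant | Significant in intervention, not in control | Welch test of change between arms |
|---|---|---|---|
| 0.1 SD | 38% | 23% | 4.9% |
| 0.2 SD | 91% | 8% | 4.8% |

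The plan adjusts for the design effect, so the within-arm rates would be lower. As a rough check, let change scores carry the same design effect of 2.60. The SE of the mean change is √(0.58 × 2.60 / 162) = 0.0965 SD.

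- 0.2 SD rise: z = 0.2 / 0.0965 = 2.07, so the intervention arm is significant in about Φ(2.07 − 1.96) = 54% of trials. The split pattern occurs in 0.545 × 0.455 = 25%.
- 0.1 SD rise: z = 1.04, giving about 18%, and 0.179 × 0.821 = 15% for the split pattern.

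The cluster adjustment reduces the first rate but does not turn a within-arm test into a test of the programme.

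**The case against.** The strongest reply is that the sentence is merely condensed. It lists two comparisons and two tests, and the variance condition speaks of two comparison groups, most naturally the two arms. So the authors probably mean Welch between arms and paired t within arms. The baseline sentence uses independent-sample tests, so they do not regard the arms as paired, and a paired test on unmatched students could hardly be run. On that reading the inflated standard errors in step 3 never arise.

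This is plausible and limits the practical harm, but the sentence does not say it. Even so read, it leaves the equal-variance comparison after baseline without a test, and change is still tested only arm by arm.

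A reader might go further and infer that the plan does not estimate the intervention-versus-control effect at all. The document does not support that. The difference between the arms is the first comparison named in the sentence, a Welch test of post-intervention scores would estimate it, and the sample size is consistent with a two-arm comparison.

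Two more points for the plan stand. Nothing in it says that a within-arm result will be read as efficacy, and 2.5 is a statement of expectation, not a decision rule. It gives no figure for a rise among controls either. A full analysis plan, not shown, could add a baseline-adjusted model. That would not correct the rule printed in 2.4, which is faulty as it stands and not just brief.

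**Conclusion.** The concern holds in a limited form. The rule in 2.4 makes the choice of test depend on variance when it should depend on pairing, and it merges between-arm and within-arm comparisons. The plan lists a between-arm difference in mean scores, but names no between-arm test of change and no baseline-adjusted contrast, and 2.5 describes success by the intervention arm alone.

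The size is conditional. The SE inflation of 1.20 to 1.86 applies only if Welch is used on the same students' scores, with r between 0.3 and 0.71. The risk of a false conclusion applies only if a within-arm rise is taken as efficacy and scores also rise in controls. For a common rise of 0.1 to 0.2 SD, the intervention arm alone would then look effective in 38% to 91% of trials ignoring clustering, or roughly 18% to 54% with a design effect of 2.60, against about 5% for a between-arm test of change (simulated without clustering). The sample size is unaffected.

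**What to change.** Replace the test sentence in 2.4 with three statements:

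1. For each scale and post-intervention time, the effect estimate is the intervention-minus-control difference, adjusted for the baseline score already collected and allowing for clustering by school, with a 95% CI.
2. The between-arm comparison uses an independent-sample method whatever the variances.
3. Within-arm changes are reported descriptively, as paired differences, without p-values offered as evidence of efficacy.

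Reword 2.5 so that the expected outcome is higher depression literacy in the intervention than in the control schools.

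The cost is a change of wording and slightly more analysis work, with no new data and no change in sample size. One drawback should be stated openly: with four schools in two arms, inference at school level has about 4 − 2 = 2 degrees of freedom, so the intervals will be wide. Correcting the test rule does not remove that limit.

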### Sampling size and design

2.2

The sample size calculation will be conducted to determine the number of participants required. Based on the study's design, an intracluster correlation coefficient (ICC) of 0.02 will be used in sample size calculation based on similar studies,^[15,16]^ and an effect size of 0.5 will be used to detect the medium effect of the intervention based on similar studies by Perry et al^[15]^ and Gulliver et al,^[13]^ which used the same design and assessment tool (the depression literacy questionnaire [D-Lit]). Other parameters for estimating sample size include a 95% confidence interval and an Alpha coefficient of 5%. Accounting for a 10% non-response and/or drop-out rate, the total required sample size will be 360 students, 180 of whom will be recruited for the intervention group and 180 for the control group. The unadjusted sample size calculation will be conducted using the G∗Power program (version 3.1.9.1; Heinrich Heine Universität, Düsseldorf, Germany)^[17]^, then adjusted for the cluster design effect according to the methods outlined in Campbell et al.^[18]^

For sampling procedures in stage one 13 secondary schools in Jazan city will be stratified according to sex (6 schools for boys and 7 schools for girls). In stage two, 1 school from each stratum will be selected at randomly for the control group, and another one from each stratum will be selected at randomly for the intervention group using the closed envelope technique. Finally, in sage three and based on the calculated sample size of 360, random sampling technique will be used to recruit 180 students from the control schools (1 boy's school and 1 girl's school) and 180 students from the intervention schools (1 boy's school and 1 girl's school) (see Figure 1, Supplemental Content which illustrates the sampling procedures).

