#### Phase one

2.3.1

Pre-intervention assessment through the D-Lit, the depression stigma scale (DSS), and the self-stigma depression scale (SSDS) will be carried out for the control and intervention groups to establish a baseline information. Participants will be asked to provide basic demographic information (sex, age, grade, school level, residence, and nationality).

The D-Lit assesses mental health literacy specific to depression. The instrument was developed by the National Institution for Mental Health Research in Australia, lead developer Kathy Griffiths. The D-Lit questionnaire's Cronbach alpha is 0.70, and its test–retest reliability is *r* = 0.71.^[13]^ The questionnaire consists of 22 true-or-false items. Respondents can answer each item with 1 of 3 options: “true,” “false,” or “don’t know.” Each correct response receives 1 point. Higher scores indicate higher mental health literacy of depression. D-Lit items are about depression symptoms, management, treatment, and duration, as well as differentiation between depression and other mental illnesses.

The DSS is designed to measure stigmas associated with depression. The scale was developed by the National Institution for Mental Health Research in Australia, lead developer Kathy Griffiths. The DSS has 2 subscales, which measure 2 different types of stigma: personal and perceived. The Personal Stigma Subscale measures stigma in the respondents’ own attitudes towards depression by asking them to indicate how strongly they personally agree with 9 statements about depression. The Perceived Stigma Subscale measures the respondent's perception about the attitudes of others towards depression by asking them to indicate what they think most other people believe about the same 9 statements. Responses to each item are measured on a 5-point scale (ranging from 0, “strongly disagree” to 4, “strongly agree”). Higher scores indicate higher levels of depression stigma. Cronbach alpha values for the total, personal, and perceived depression stigma scales were 0.78, 0.76, and 0.82, respectively.^[19]^

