### Ethical consideration

2.6

This study protocol was approved by a Faculty of Medicine Research Ethics Committee at Jazan University. Consent will be received from the managers of the selected schools. Before participation, students will be informed that the collected information will be kept anonymous and that participation is absolutely voluntary. The participants will be assured that they could withdraw from the study at any time. Informed consent will be sought from the eligible participants following a full disclosure regarding the study. Proxy consent for the children will be obtained from their guardians and from each child who is eligible to participate in the study before randomization.

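### The between-arm effect on D-Lit, DSS and SSDS is tested without adjustment for each student's baseline score, although those scores are measured in both arms

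*Protocol article*

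**What the plan says.** Section 2.3.1 collects the three scales in both arms before the intervention: "Pre-intervention assessment through the D-Lit, the depression stigma scale (DSS), and the self-stigma depression scale (SSDS) will be carried out". Section 2.3.3 repeats them immediately afterwards and at 3 and 12 months.

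Section 2.4 then names the tests:

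- Arm means, and change over time within each arm, are tested by a paired t test, or by Welch's t test if variances differ.
- Baseline scores are compared between arms by Student's t or Mann–Whitney test. The stated purpose begins "To examine differences between groups at the baseline".
- Socio-demographic variables are compared by chi-squared tests.
- A design effect is the only adjustment named.

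On the design, section 2.2 says "13 secondary schools in Jazan city will be stratified according to sex", and one boys' and one girls' school is drawn for each arm. Section 2.6 says "students will be informed that the collected information will be kept anonymous".

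**The concern.** The text fixes an effect analysis, and that analysis leaves out the most informative covariate the trial collects. A significance test at baseline does not remove a difference and does not improve precision. With four schools, a non-significant result says little about comparability. The within-arm paired tests do use each student's baseline, but they give no contrast between arms: a significant change in one arm and not in the other is not an estimate of the intervention effect.

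With two schools per arm, the arms can start some distance apart by the draw of schools alone. Part of that distance reappears in the follow-up means and is read as effect, or hides one. Precision is also given up although the data needed are already being collected.

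**Working it through.** **Inputs.** Section 2.2: "an effect size of 0.5 will be used to detect the medium effect"; "an intracluster correlation coefficient (ICC) of 0.02 will be used in sample size calculation"; alpha 5% (taken as two-sided); 10% loss; 180 students and two schools per arm. Section 2.3.2.1: 90 students per intervention school, so 81 per school and 162 per arm after 10% loss. Section 2.3.1: D-Lit test–retest r = 0.71. Power is not stated; the text has instead "Other parameters for estimating sample size include a 95% confidence interval". I assume 80%.

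**1. The plan's own sample size.** A standardised difference of 0.5 at 80% power needs 63 per arm (normal) or 64 (t). The design effect is 1 + (81 − 1) × 0.02 = 2.60.

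- Normal: 2 × 63 × 2.60 / 0.9 = 364
- t: 2 × 64 × 2.60 / 0.9 = 370

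The stated 360 is within 3% of both, so these inputs represent the plan fairly.

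**2. Chance baseline difference between arms** (SD units).

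- Effective n per arm = 162 / 2.60 = 62.3
- SD of the difference = √(2 / 62.3) = 0.179
- 95% range = ±1.96 × 0.179 = ±0.35
- Carried into the follow-up difference at r = 0.71: ±0.71 × 0.35 = ±0.25, half of the 0.5 target
- At r = 0.5: ±0.5 × 0.35 = ±0.18

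**3. Where the variance lies.** The variance of the arm difference is 2 × (0.02/2 + 0.98/162) = 2 × (0.01000 + 0.00605) = 0.0321. The between-school share is 0.01000 / 0.01605 = 62%.

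**4. Variance after adjustment.**

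- (a) Baseline explains r² of the variance at student and school level. The factor is 1 − r²: 0.496 at r = 0.71, 0.75 at r = 0.5.
- (b) Baseline explains student-level variance only, and the school component is unchanged. At r = 0.71: 2 × (0.01000 + 0.00605 × 0.496) = 0.0260, a factor of 0.81. At r = 0.5: 2 × (0.01000 + 0.00605 × 0.75) = 0.0291, a factor of 0.91.

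**5. Power by the design-effect approach**, Φ(0.5/SE − 1.96).

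| Analysis | Variance factor | SE | Power |
|---|---|---|---|
| Unadjusted | 1.00 | 0.179 | 0.80 |
| r = 0.71, (b) | 0.81 | 0.161 | 0.87 |
| r = 0.71, (a) | 0.496 | 0.126 | 0.98 |
| r = 0.5, (b) | 0.91 | 0.171 | 0.83 |
| r = 0.5, (a) | 0.75 | 0.155 | 0.90 |

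**6. The same variances with a school-level t reference.** Four schools less two arms leaves 2 df. Power is 0.35 unadjusted; 0.41 (b) to 0.56 (a) at r = 0.71; 0.38 to 0.43 at r = 0.5. Regressing school means on school baseline means would spend one of the 2 df. Even with case (a) at r = 0.71, power on 1 df is 0.24, below the unadjusted 0.35.

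**The case against.** **An unadjusted comparison is valid.** Chance imbalance under random selection of schools is sampling variance, not bias, and the design effect already represents it. This stands: the point is about efficiency and about reading the one realised trial, not about type I error.

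**Covariates are commonly left to an analysis plan.** This does not dispose of the point. Section 2.4 names the test for the effect and the only adjustment, and a baseline-adjusted comparison would replace that test, not add detail to it.

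**The gain may be small.** This stands in part. The 0.71 is a D-Lit test–retest reliability cited from another study, not a correlation across an intervention and up to 12 months. Most of the variance is between schools, so if baseline says nothing about school differences the gain is 19% or 9%. Nor is case (b) a strict floor. If true school means varied at baseline with ICC 0.02 yet were unrelated to those at follow-up, the adjustment would carry that variation in: at r = 0.71, 2 × (0.01000 × 1.504 + 0.00605 × 0.496) = 0.0361, a factor of 1.12. That is unlikely when the same students answer the same scale, but it cannot be excluded from the article.

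**Stronger readings that the article does not support.** A reader might infer that:

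- baseline scores are used for nothing but balance tests; they also enter the within-arm paired tests;
- half the variance is lost on all three scales; that is the best case, for D-Lit alone;
- a baseline imbalance passes in full into the effect; only the fraction r does;
- ignoring the sex stratum leaves the arms unbalanced on sex; each arm has one boys' and one girls' school, so what remains is imbalance between the particular schools;
- the plan's power is 0.35; that is the power of a 2-df school-level test, which the article does not specify.

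**Conclusion.** The point holds as a worthwhile improvement to the stated analysis. The between-arm effect is unadjusted although each student's baseline score is available, and neither the baseline tests nor the within-arm paired tests supply an adjusted effect.

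For D-Lit, the realistic gain is a variance reduction of 19% to 50% if the pre-post correlation equals 0.71, and 9% to 25% if it is 0.5. The position within each range depends on whether baseline also explains differences between schools. For DSS and SSDS the article gives no correlation, so the direction is the same but the size is unknown.

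These figures assume ICC 0.02 at baseline and follow-up, 81 analysed per school, a two-sided 5% test and, for reproducing the sample size, 80% power. Adjustment does not cure the small number of schools: on 2 df, power stays at or below 0.56 for the correlations considered.

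**What to change.** In section 2.4:

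- Compare arms on each post-intervention score with the student's own baseline score on that scale as a student-level covariate, and keep the adjustment for clustering.
- Do not regress on school baseline means while there are only four schools, because of the degree of freedom it spends.
- Replace the baseline significance tests with a descriptive table of baseline scores and characteristics by arm and by school.
- A sex term is not needed to remove imbalance. With four schools it too would cost one of the 2 df in a school-level analysis.

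In sections 2.4 and 2.6: state that questionnaires are linked by a coded identifier. The adjustment needs linked records, and so do the paired tests already planned. Reconcile this with the assurance that "students will be informed that the collected information will be kept anonymous", for example by describing the data as coded and confidential.

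The cost is a few sentences of analysis text and one phrase in the information given to students. No further students or measurements are needed.

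### An unadjusted P<.05 for every analysis leaves nine implied between-arm tests unordered, and even D-Lit alone has no fixed decisive time point

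*Protocol article*

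**What the plan says.** Section 2.4 (Statistical analysis and data management plan) lists two kinds of comparison. The first is between arms: "Differences between mean scores of D-Lit, DSS, and SSDS for the intervention and control groups". The second is within arms: "as well as changes in mean scores over time for each group". The section closes with one threshold for all of them: "P*-values <.05 will be used in all analyses". It also says that every test will be adjusted for clustering by the design effect. It states no order of testing and no adjustment for the number of tests.

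Section 2.3.3 (Phase three) places the post-intervention assessments "immediately after the intervention and during a follow-up after 3 and 12-months", with all three questionnaires used in both arms.

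The article gives three indications of which result matters most:

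- Section 1 (Introduction): the main objective is to "measure the effect of an educational intervention program about depression on depression literacy and stigma", with neither ranked above the other.
- Section 2.2 (Sampling size and design): the effect size of 0.5 comes from studies described as having used the D-Lit. The remaining inputs are given as "a 95% confidence interval and an Alpha coefficient of 5" per cent.
- Section 2.5 (Expected outcome): "The expected outcome of this study is an increase in depression literacy" in the intervention group. Stigma is not mentioned, and no scale or time point is given.

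**The concern.** This is a rule that the article states, not a detail it leaves out. Applied as written, each scale at each time is judged at 5% on its own, and nothing says which comparison carries the conclusion. The chance of some false between-arm difference then exceeds 5% by an amount that depends on correlations the article does not give.

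The sections also lead to different readings of the same data. A difference on a stigma scale at 12 months alone would bear on the objective in section 1 and pass the threshold in section 2.4. Yet it is neither the outcome expected in section 2.5 nor the one behind the effect size. Even with attention confined to D-Lit, the time point that counts could be chosen after the results are known.

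**Working it through.** **Inputs**

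- Level per test: 0.05 (section 2.4), taken as two-sided; sidedness is not stated.
- Scales compared between arms: 3 (section 2.4).
- Post-intervention times: 3 (section 2.3.3).
- Implied between-arm tests: 3 × 3 = 9. The article does not write this number; it comes from reading sections 2.3.3 and 2.4 together. Within-arm tests are not counted.
- Effect size 0.5 SD, ICC 0.02, 10% loss, 180 students per arm (section 2.2); 90 students per intervention school (section 2.3.2.1), hence 81 after 10% loss.
- Correlations between scales and between times: not given, so assumed.
- Power: not given, so 80% assumed.

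**Step 1. The plan's own figure, 360.** Two-sided 5% and 80% power at 0.5 SD need 2 × (1.960 + 0.842)² / 0.5² = 62.8, so 63 per arm (64 by the t test). The design effect is 1 + (81 − 1) × 0.02 = 2.6. Then 63 × 2.6 / 0.9 = 182 and 64 × 2.6 / 0.9 = 185 per arm, or 364–370 in total. This is within 3% of 360, so the size is compatible with one comparison at an unadjusted 5%. The match does not prove that this is how 360 was reached. Other combinations also fit, for example 95% power with 30 per cluster.

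**Step 2. Chance of at least one false positive, independent tests.** The formula is 1 − 0.95^k.

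- k = 3 (D-Lit at three times): 1 − 0.95³ = 14.3%.
- k = 9 (three scales at three times): 1 − 0.95⁹ = 37.0%.

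**Step 3. The same with correlated tests.** These come from 400,000 multivariate-normal draws per setting, two-sided 5% per test, with one common correlation.

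| Assumed correlation | Nine tests | D-Lit at three times |
|---|---|---|
| 0.3 | 32.6% | 13.7% |
| 0.5 | 26.9% | 12.6% |
| 0.7 | 20.3% | 10.9% |
| 0.8 | 16.6% | 9.8% |

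With separate correlations, 0 to 0.5 between scales and 0.5 to 0.8 between times, nine tests give 23.5% to 33.1%. The two sets together span 16.6–33.1%. At a common correlation of 0.9, which is higher than I would assume, the nine-test figure is still 12.3%.

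**Step 4. Power once a primary is named.** Analysed students per arm: 180 × 0.9 = 162; effective number 162 / 2.6 = 62.3. Power is Φ(0.5 × √(62.3/2) − z) = Φ(2.791 − z).

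- One test at 0.05 (z = 1.960): 79.7%.
- Three tests by Bonferroni, 0.0167 each (z = 2.394): 65%.
- Nine tests by Bonferroni, 0.0056 each (z = 2.773): 51%.

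Naming one primary comparison therefore holds the error at 5% without loss of power. A flat adjustment over all nine would be expensive.

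**The case against.** The strongest reply is that this is a condensed article. The full protocol and any separate analysis plan are not shown, and the abstract has no text in the copy at hand. Endpoint ranking and multiplicity control are often left to such documents. That stands to this extent: the lack of a named primary endpoint is not in itself the finding. It does not dispose of the stated rule, which covers all analyses and would have to be reconciled with any adjustment made elsewhere.

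Four stronger readings are tempting, and the article does not support them.

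- A reader might infer that any one of the nine results below .05 would count as success. Section 2.4 gives no rule for what supports a conclusion, and sections 2.2 and 2.5 point to D-Lit.
- A reader might take 37%, or any narrow range near it, as this trial's error rate. It assumes independence, which is implausible for repeated scores on the same students. All the figures also assume that each test holds its own 5%, which with two schools per arm depends on the cluster adjustment and is a separate question.
- A reader might add the DSS and SSDS subscales to the count. They appear only where the instruments are described; section 2.4 does not plan to test them.
- A reader might conclude that the immediate assessment is the intended main one. Nothing in the article favours it over 3 or 12 months.

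It can also be said that section 3 presents positive trends as support for further, larger work. That lowers the stakes but does not remove the need to know which comparison is decisive.

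**Conclusion.** The concern holds in this limited form. The article applies an unadjusted 5% level to nine implied between-arm tests without ordering them, and its sections differ on whether stigma ranks equally with literacy.

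If each test holds its level, the chance of at least one false-positive between-arm result is 37.0% under independence and 16.6–33.1% under the assumed correlations. On the reading kindest to the plan, with literacy as the implied main outcome, it is about 10–14%, because the decisive time point is left open. The excess over 5% appears throughout the range tried; its exact size cannot be known from the article. This should be corrected before the data are seen, but the conduct of the trial need not change.

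**What to change.** In section 2.4, replace the blanket threshold with an ordered plan:

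1. One primary between-arm D-Lit comparison at one time point, tested at 5%. The investigators should choose the time and fix it before the data are seen; immediately after the intervention is one example.
2. D-Lit at the other two times in a stated fixed sequence, each at 5%, stopping at the first non-significant result.
3. DSS and SSDS totals as secondary, with Holm adjustment over one defined family of 2 scales × 3 times = 6 tests.
4. Within-arm changes reported descriptively.

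State whether the Holm family is opened only after the whole D-Lit sequence succeeds. If it is tested regardless, each family is held at 5% separately and the two together are bounded by 5% + 5% = 10%.

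Align sections 1, 2.4 and 2.5 with this order.

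**Cost.** No added students, visits or instruments, and about 80% power is kept for the primary comparison under the step 4 assumptions. The downside falls on stigma. It becomes secondary to literacy, which changes the emphasis of the stated objective, and its smallest P-value must be below 0.05 / 6 = 0.0083. At that threshold (z = 2.638), a single 0.5 SD effect has power Φ(2.791 − 2.638) = 56%.
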